### Monitoring

The data monitoring committee (DMC) consists of a critical care physician, nephrologist, and cardiovascular expert, all experienced in clinical research. The principal investigator will report the process of the trial, quality of data collected, adverse events, and protocol deviation and violation to the DMC. The DMC will meet every 6 months during the conduction of the trial. No interim analysis for efficiency is planned as the assumptions in sample size calculation are less likely to be changed.

An investigator meeting is held annually to communicate the progress, quality control, and approaches to improve recruitment and address any quality of data issues.

### Trial status

There have been 89 patients enrolled at 10 hospitals in study A, and the enrollment is still ongoing. However, study B was stopped in August 2019 in the absence of any patients being enrolled. Although we aimed to test the hypothesis that beta-blockers would protect the myocardium in ECMO patients, we found this too challenging to undertake as these patients have low BP, which is a contraindication to such treatment and raised concerns of harm among investigators. Moreover, the short time window for enrollment was another barrier to recruitment, and by the time a patient is stable and without vasopressors, it is near the time to wean them off ECMO. Consequently, we decided to close recruitment into arm B. During the COVID pandemic, patient enrollment has become more challenging. A review of the feasibility of the trial will be made by the Steering Committee at the end of 2022.

## Discussion

Being one of the most seriously ill groups in clinical practice, with high mortality and requiring heavy use of critical care resources, there are considerable challenges to generate reliable evidence to guide the management of ECMO patients. Our ELITE trial attempts to address two important clinical questions with strong pathophysiological mechanisms.

A multicenter retrospective cohort study has shown that FO is common in a pediatric population (peak FO ≥ 10% in 84.8%, ≥ 20% in 67.2%, and ≥ 50% in 29%) [20] where FO has consistently been shown to be associated with adverse outcomes [21–23], while a meta-analysis of observational studies has shown lower mortality in those who receive CRRT [24]. These data suggest that early initiation of CRRT to avoid FO in the context of ECMO may be beneficial. The Kidney Interventions During Membrane Oxygenation (KIDMO) study showed that CRRT use was 43%, 16%, and 35% of patients for FO, for FO prevention, and for AKI, respectively, after ECMO [25]. However, there has not been a randomized trial to support these approaches. So, we designed this ELITE trial. As the closing of arm B, the question of whether beta-blocker is efficient in patients with ECMO remains unaddressed, and more effects should be made.

Other limitations of our trial include the lack of blinding, and for practical reasons, recruitment has been slow due to the small number of patients receiving ECMO despite the expectation of a least 10 cases treated annually across our network of 30 ICUs in China. We did not stratify our randomization by ECMO centers but will perform a subgroup analysis to explore the effect between small and large centers.

In summary, the ELITE trial is the first randomized controlled trial of critically ill patients receiving ECMO support, powered to test the effects of early CRRT versus conventional timing of CRRT on 30-day mortality. The results should inform the management of this important patient group.

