## Methods

### Study design (Fig. 1)

ELITE is a prospective, multi-center, open-label, randomized controlled trial, with a 2 × 2 partial factorial design to evaluate whether early CRRT support and beta-blockade will reduce 30-day mortality in a broad range of ECMO patients admitted to hospitals in China from July 2018. In arm A, patients are randomized to early CRRT within 24 h of initiation of ECMO or to control, regardless of whether there is a conventional indication, or to the control where patients only receive CRRT according to a conventional indication. In arm B, patients are randomized to the intravenous esmolol group or usual care. The trial design and protocol adhere to the Recommendations for Interventional Trials (SPIRIT) criteria [19] (Table 1) and checklist in Table 5 in Appendix. The study is planned to enroll patients from 10 centers in China (see Table 5 in Appendix for the hospital list).

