### Sample size

Sample size calculation is performed using the software PASS 15.0.5 based on the following assumption: a 70% 30-day mortality in the control group and a 20% relative risk reduction for each intervention (early CRRT and beta-blocker). The estimate of the intervention’s effect size was based on clinical expertise and the clinical significance of an intervention, no loss of follow-up or crossover, and 5% type I error and 20% type II error. We assume no interaction between interventions, as the overlap of the time of interventions would be limited and no carry-on effect expected. A total of 496 patients (248 per group) are required for each arm.

To achieve adequate participant enrolment to reach the target sample size, the study will be conducted at 10 high-volume centers in China. A smartphone application has been developed to facilitate randomization at the emergency room.

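### The Discussion calls the trial powered for 30-day mortality without qualification, while the same article reports 89 of 496 patients enrolled; power at sizes of 89 to 200 is 28% to 54%

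*Protocol article*

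**What the plan says.** The closing summary of the Discussion describes the trial as "powered to test the effects of early CRRT versus conventional timing of CRRT on 30-day mortality", with no condition attached.

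The basis for that description is the Sample size section. It assumes "a 70% 30-day mortality in the control group and a 20% relative risk reduction for each intervention", with 5% type I error, 20% type II error and no loss to follow-up or crossover, and concludes: "A total of 496 patients (248 per group) are required for each arm". On delivery it says: "To achieve adequate participant enrolment to reach the target sample size, the study will be conducted at 10 high-volume centers in China".

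Enrolment is of patients "admitted to hospitals in China from July 2018" (Study design). The Trial status section reports: "There have been 89 patients enrolled at 10 hospitals in study A, and the enrollment is still ongoing". It gives no date for that count. It adds that the pandemic has made enrolment harder, and then: "A review of the feasibility of the trial will be made by the Steering Committee at the end of 2022". The Discussion lists slow recruitment among the limitations, set against "the expectation of a least 10 cases treated annually across our network of 30 ICUs in China".

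**The concern.** Power belongs to the size a trial actually reaches. When the article was written, study A had 89 of 496 patients, all 10 planned hospitals had contributed, and the investigators were themselves about to review whether the trial was feasible. A closing sentence that calls the trial powered, without saying at what size, does not fit that status.

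What is at stake is how the result will be read. If recruitment closes well short of target, a non-significant comparison is the likelier outcome even if early CRRT has the full planned effect, at least up to about 150 patients; at 200 it is close to an even chance. Presented as the result of a powered test, such a finding could be taken as evidence against early CRRT when the data would be compatible with the planned benefit. The article discloses slow recruitment, but not what it does to power.

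**Working it through.** **Inputs.** Control mortality 70% and 20% relative reduction, so 0.70 × 0.80 = 56%; type I error 5%, type II error 20%; 496 patients, 248 per group (Sample size). Two-sided tests and a log-rank primary comparison (Statistical analysis). 1:1 allocation (Randomization). Enrolment from July 2018 (Study design). 89 enrolled (Trial status).

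**1. The plan's own figure.** Pooled-variance formula for two proportions, with p̄ = 0.63 and difference 0.14:

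n per group = [z(0.975)·√(2·0.63·0.37) + z(power)·√(0.70·0.30 + 0.56·0.44)]² / 0.14²

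- 80% power: (1.960 × 0.6828 + 0.8416 × 0.6756)² / 0.0196 = 185.5, so 186 per group, 372 in total.
- 90% power: (1.960 × 0.6828 + 1.2816 × 0.6756)² / 0.0196 = 247.8, so 248 per group, 496 in total.

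The stated 496 therefore matches 90% power, not the stated 80%. With a continuity correction, 80% needs 400 in total. A log-rank calculation with hazard ratio ln(0.44)/ln(0.30) = 0.682 needs about 342 to 350. This mismatch is a separate matter, but it means two targets have to be carried below: 496 and 372.

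**2. Power and precision at smaller sizes.** With n = N/2:

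Power = Φ{[0.14·√n − 1.960 × 0.6828] / 0.6756}

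95% CI half-width for the risk difference = 1.96·√(0.4564/n)

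Log-rank power (Schoenfeld, events = 0.63·N) = Φ{0.3829·√(events/4) − 1.96}

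| N | Power, two proportions | Power, log-rank | CI half-width |
|---|---|---|---|
| 89 | 28% | 30% | 20 points |
| 100 | 30% | 33% | 19 points |
| 150 | 43% | 46% | 15 points |
| 200 | 54% | 57% | 13 points |
| 372 | 80% | 83% | 10 points |
| 496 | 90% | 92% | 8 points |

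Example at N = 89: (0.14 × √44.5 − 1.338)/0.6756 = −0.598, and Φ(−0.598) = 0.275; half-width 1.96 × √(0.4564/44.5) = 0.198. At 89 and at 150 patients the half-width exceeds the planned 14-point difference. At 89, mortality would have to fall to about 41% for 80% power. None of these figures depends on when the count was taken.

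**3. Distance to target.** 89/496 = 17.9%. Still needed: 496 − 89 = 407, or 372 − 89 = 283 for 80% power. The count is undated. The text mentions the pandemic and treats the end of 2022 as future, so I assume a date between mid-2020 and the end of 2022, and a constant average rate from July 2018.

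| Assumed count date | Months | Rate per year | Years to 496 | Years to 372 |
|---|---|---|---|---|
| mid-2020 | 24 | 44.5 | 9.1 | 6.4 |
| end 2020 | 30 | 35.6 | 11.4 | 7.9 |
| end 2021 | 42 | 25.4 | 16.0 | 11.1 |
| mid-2022 | 48 | 22.3 | 18.3 | 12.7 |
| end 2022 | 54 | 19.8 | 20.6 | 14.3 |

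Example: 89/2 years = 44.5 a year; 407/44.5 = 9.1 years.

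**The case against.** The best reply is that *powered* ordinarily describes the planned size, and that nothing is hidden: the count of 89 appears in both the Abstract and the Trial status section, slow recruitment is listed as a limitation in the paragraph just before the quoted sentence, and a feasibility review is dated and assigned to the Steering Committee. That stands as far as enrolment is concerned; a reader is not misled about the count. It does not settle the wording, because the sentence is an unconditional summary of the trial as it stands and nowhere gives the power at a smaller size.

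Four stronger readings are tempting, and the article does not support them.

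- *The target is two decades away.* That is the top of the range. It needs a count taken in 2022 and a constant rate. The article dates neither the count nor the opening of each hospital.
- *The objective cannot be tested.* That prejudges a review that had not yet happened, and it takes 496 as the size needed although about 372 gives the stated 80%.
- *The centres could never have supplied the patients.* The sentence about 10 cases a year across 30 ICUs may mean per ICU or in total, and the article does not say how the 30 ICUs relate to the 10 hospitals. No capacity argument can rest on it.
- *The feasibility review will bias the estimate.* Nothing says the Steering Committee will see outcomes by group. The Monitoring section plans no interim efficacy analysis and provides for six-monthly data monitoring committee meetings and annual investigator meetings on recruitment. Which data the review uses, and how a truncated trial is to be interpreted, may properly sit in the full protocol or SAP, so their absence from an article is no fault.

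**Conclusion.** The point holds as one of wording. The unconditional power claim in the Discussion does not agree with the article's own trial status. If the trial closes at 89 to 200 patients, power for the planned effect is 28% to 54% by the two-proportion calculation (30% to 57% for the log-rank test under proportional hazards), with a 95% CI half-width of 20 to 13 percentage points against a planned difference of 14.

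The power figures rest only on the plan's stated rates and error levels. The range of 89 to 200 is illustrative; the article gives no revised target. The projection of roughly 9 to 21 further years to 496, or 6 to 14 to about 372, rests on two assumptions that the article does not supply: a count date between mid-2020 and the end of 2022, and a constant average rate. Even the shortest of these supports qualifying the claim. It does not show that the design is invalid or that the target is unattainable.

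**What to change.** 1. In Trial status (and the Abstract), give the date to which the count of 89 refers.
2. In the Discussion, make the claim conditional: the trial would have the planned power if the target is reached. The power quoted there must match the target, that is about 90% at 496 or 80% at about 372 on the stated assumptions.
3. Beside it, give power and 95% CI half-width at realistically reachable sizes, for example 28% and 20 points at 89, 30% and 19 points at 100, 43% and 15 points at 150, 54% and 13 points at 200. A non-significant result from a truncated trial would then not be presented as coming from a powered test.

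The cost is text only: no added patients, procedures or analyses. The drawback is that the stated power becomes less favourable.

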## Data Availability

The datasets used and analyzed during the current study are available from the corresponding authors on reasonable request.

